## Abstract

*Objective*. The RNAFH study (effect of rosuvastatin on nonalcoholic fatty liver disease in metabolic syndrome patients without overt diabetes evaluated by ^1^H-MRS) is a prospective randomized, single-center, open-label trail designed to assess the effect of rosuvastatin on the intrahepatocellular lipid (IHCL) level of nonalcoholic fatty liver disease (NAFLD).* Methods*. 40 NAFLD patients meeting inclusion and exclusion criteria with metabolic syndrome (MS) but without overt diabetes mellitus will be included. Patients will be randomized to 52-week treatment with either rosuvastatin (10 mg/d) or blank control. The primary end point is IHCL evaluated by ^1^H-MRS, which was considered to be the most accurate noninvasive method for the evaluation of NAFLD. Secondary end points include homeostasis model assessment of insulin resistance (HOMA-IR) index on behalf of insulin resistance level and lipid parameters. Safety indicators will be monitored such as liver function, renal function, muscle stability, and glucose metabolism. The aims of the present study are noteworthy in respect that (1) IHCL is a quantitative indicator for evaluating the degree of fatty liver disease and ^1^H-MRS is a noninvasive technique to provide this specific index precisely, (2) meanwhile the HOMA-IR index and lipid parameters will be monitored, and (3) the safety of rosuvastatin treatment for 52 weeks will be evaluated including glucose metabolism, muscle stability, liver function, and renal function.

## 1. Introduction

Nonalcoholic fatty liver disease (NAFLD) refers to the presence of hepatic steatosis without other causes (e.g., heavy alcohol consumption) that can be found for secondary hepatic fat accumulation. NAFLD may progress to cirrhosis and is likely one of the most important causes of cryptogenic cirrhosis [1]. NAFLD is seen worldwide with the prevalence increasing over time and the major risk factors include central obesity, dyslipidemia, and impaired glucose metabolism which are also the main components of metabolic syndrome (MS) [2, 3]. The close relationship between NAFLD and MS has been demonstrated in a previous study, which showed that MS was associated with an increased risk of severe nonalcoholic fatty liver fibrosis (OR 3.5, 95% CI 1.1–11.2) [4]. On the other hand, NAFLD was an independent risk factor in the development of type 2 diabetes, especially in normal weight individuals with prediabetes. In addition, NAFLD has an important role in the pathogenesis of cardiometabolic diseases. It has also been demonstrated to be the strongest determinant of increased carotid intima-media thickness, which can stratify cardiovascular risk [5]. So far, there is no widely accepted pharmacologic treatment for NAFLD. The traditional treatment includes pioglitazone, a type of insulin-sensitizing agent, which could improve liver biochemical and histological parameters in patients with nonalcoholic steatohepatitis (NASH). However, its use was associated with adverse events, such as weight gain and swollen legs [6–10]. RCT studies with new agents have been conducted, but more extensive trials with larger sample size are needed. For example, liraglutide is a type of glucagon-like peptide 1 receptor agonist, which could resolve definite NAFLD and prevent the progression of fibrosis [11]. Elafibranor is an agonist of the peroxisome proliferator-activated receptor-*α* and receptor-*δ*, but its effect on NASH patients was uncertain, depending on the model of analysis [12]. The bile acid derivative 6-ethylchenodeoxycholic acid (obeticholic acid) is a potent activator of the farnesoid X nuclear receptor, which was shown to improve the liver histology of NASH patients proven by biopsy, but its long-term benefits and safety need further clarification [13].

A few RCT [14–17] studies have shown that the statins, the inhibitor of 3-hydroxy-3-methylglutaryl-coenzyme A (HMG-CoA) reductase, can improve the structure or liver function indices in patients with NAFLD and NASH. And also, they are safe to use in patients with chronic liver diseases and compensated cirrhosis even at high dose [16–18]. A recent observational study showed that statin use was protective from liver steatosis, steatohepatitis, and fibrosis stage in patients negative for the I148M variant [19]. Conversely, negative findings were also obtained in RCT19 where patients with biopsy-proven NASH were randomized to simvastatin versus placebo. However, these data were not convincing enough because (1) the sample size was too small [14, 16, 20] or the study duration was too short [16], (2) the other oral drugs like Vitamin C and Vitamin D were simultaneously taken, which might become the confounding factors [14], (3) diagnostic method was not accurate enough [14, 15], and (4) the primary end point was not the change of liver fat content or resolution of NAFLD or NASH [16, 17]. Further RCTs of adequate size and duration are required in the future.

## 2. Methods

### 2.1. Study Design

The RNAFH study is a prospective randomized, single-center, open-label study. This investigator-driven study is supported by AstraZeneca. In order to rule out confounding factors and meet the ethical standards to the maximum extent, this study excluded patients with overt diabetes. Interestingly, a very similar study was undertaken, which demonstrated that an inhibitor of 11 beta hydroxysteroid dehydrogenase type 1 (HSD1), namely, RO5093151, could decrease liver fat content in NAFLD patients. In that study NAFLD was also defined by ^1^H-MRS without liver biopsies, and diabetes patients were excluded because various diabetes treatments made it difficult to match the two groups [21].

In addition, ^1^H-MRS was currently confirmed to be the most sensitive, specific, noninvasive, and no-radiation method for the diagnosis of NAFLD, compared with CT, MRI, or US; the most attractive advantage was quantitative measurement of intrahepatocellular lipid (IHCL) [22]. Also, the reproducibility of this procedure was validated by duplicate hepatic triglyceride content measurements highly correlated and the coefficient of variation below 10%. The 95th percentile of IHCL in normal subjects was 5.56% [23]. It is known that NAFLD patients receive very different prognoses, depending on the degree of severity. Patients with mild disease are usually not eligible for pharmacologic therapy; instead the disease should be managed through dietary and lifestyle changes [12] Histological grade 1 of NAFLD (5%–33% macroscopic liver fat) corresponds to IHCL value of 11% [24]. According to this, only the patients with IHCL value above 10% are considered to have moderate to severe degree of liver steatosis. Therefore, the RNAFH study was focused on the effect of rosuvastatin on this group of patients with moderate to severe degree of NAFLD.

At maximal prescribed doses, rosuvastatin has the highest capacity for LDL-cholesterol (LDL-C) reduction and triglycerides (TG) lowering among the statins. Moreover, rosuvastatin has better absorption rate and bioavailability, and it is hydrophilic and hence associated with less adverse events [25]. In addition, rosuvastatin has similar or even less risks of hepatic dysfunction compared with other statins. So rosuvastatin is the most potent and relatively safe agent to choose in this study [25–27]. According to a recent meta-analysis, the risks of diabetes with satins versus placebo (OR 1.11) and intensive versus moderate intensity statin therapy (OR 1.12) were both within the acceptable range [28].

Approval of the protocols and informed consent forms was obtained from the institutional ethics committee of the Peking Union Medical College Hospital of Chinese Academy of Medical Sciences. This study has been registered in Clinical Trails.gov (ChiCTR-IPR-15007014).

### 2.2. Study End Points

This study is to explore the effect of rosuvastatin 10 mg/d on intrahepatocellular lipid (IHCL) in nonalcoholic fatty liver disease (NAFLD) patients with metabolic syndrome (MS) but without overt diabetes. The primary end point is the change of IHCL evaluated by ^1^H-MRS. Secondary end points are (1) lipid parameters including CHO (cholesterol), LDL-C (low density lipoprotein cholesterol), HDL-C (high density lipoprotein cholesterol), TG (triglyceride), and FFA (free fatty acid) and (2) HOMA-IR index calculated by fasting blood glucose (FBG) multiplied by fasting insulin (FINS) divided by 22.5. The safety indices are including ALT (alanine aminotransferase), AST (aspartate transaminase), CK (creatine kinase), TBIL (total bilirubin), FBG (fasting blood glucose), FINS (fasting serum insulin level), HbA1c (hemoglobin A1c), Scr (serum creatinine), UACR (urine albumin-creatinine ratio), and eGFR (estimated glomerular filtration rate).

### 2.3. Inclusion and Exclusion Criteria

40 NAFLD patients from the outpatient department of Peking Union Medical College Hospital meeting the criteria between January 2016 and January 2017 will be enrolled. All patients assessed for eligibility will be registered. Inclusion and exclusion criteria are shown as follows:Inclusion criteria
Provision of informed consent prior to any study specific proceduresMen and female adults aged 18–70 years who agree to use contraceptive methods to prevent pregnancy while enrolled in studyPatients fulfilling the diagnostic criteria of MS of IDF in 2006 [3] (central obesity is an essential element (increased waist circumference which is ≥90 cm in Chinese men or ≥80 cm in women) plus any two of the following: TG > 1.7 mmol/L; HDL < 1.03 mmol/L in men or <1.29 mmol/L in women; SBP > 130 mmHg, DBP > 85 mmHG, or treatment for hypertension; FBG > 5.6 mmol/L)The diagnosis of NAFLD screened by abdominal ultrasound and confirmed by ^1^H-MRS with IHCL > 10%No overt diabetes history and FBG < 7.0 mmol/L plus HbA1C < 6.5%Statins not used within past 3 months or currently taking fibratesThe patients without history of arteriosclerotic cardiovascular disease (ASCVD)
Exclusion criteria
Women planning to get pregnant within 1 year or being pregnantTSH (thyroid stimulating hormone) > 10 uU/mLAlcohol consumption per week >14 U (140 g) in women or >21 U (210 g) in men.Positive results for any of HBsAg, HCV-Ab, and HIV-Ab or any other chronic or acute liver diseasesALT or AST > 2 ULN (upper limits of normal) or TBIL > 2 ULN or CK > 2 ULNeGFR (EPI) <30 mL/minLDL-C < 70 mg/dL or LDL-C > 190 mg/dLTG > 5.6 mmol/LAllergy history of statinssystemic or inhalative steroid use within one yearPatients with active or chronic myopathy.

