### 2.4. Study Procedure

The study flow is shown in Figure 1. Patients will be randomly assigned to receive rosuvastatin 10 mg/day (*n* = 20) or blank control (*n* = 20). All patients will be given lifestyle improvement suggestions at baseline. ^1^H-MRS will be conducted at the baseline and the 52nd week; the images of ^1^H-MRS are shown in Figure 2. Physical examination and ALT, AST, TBIL, eGFR (EPI), CK, Cr, ACR (urine), TSH, FBG, FINS, LDL-C, HDL-C, TC, TG, and FFA will be measured at the baseline, 4th, 16th, 28th, and 40th week, and 52nd week. Lifestyle improvement suggestions include reducing oil consumption, weight loss, increasing aerobic exercise, smoking cessation, and alcohol reduction. The lifestyle intervention should be recorded at each visit, including food frequency questionnaires and amount and intensity of exercise. The change of IHCL will be calculated by Siemens SKYIA 3.0 T using HISTO-MRS placed on the same region of right lobe of liver at baseline and at end point. Figure 2 showed the ^1^H-MRS images of one patient enrolled in this study with IHCL > 10%.

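### The statin/fibrate inclusion line in Section 2.3 has two readings with opposite eligibility decisions; read literally, it admits current fibrate users

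*Protocol article*

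**What the plan says.** **Lipid drugs.** The line is in the inclusion list of Section 2.3. Its first half requires that statins were not used in the past 3 months. Its second half, joined by 'or', names current fibrate use and carries no 'not' of its own. The exclusion list does not mention fibrates or earlier statin use. Its only item on prior drug use is systemic or inhaled steroids within one year; allergy to statins is a separate item.

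**Diabetes.** The inclusion list requires "No overt diabetes history and FBG < 7.0 mmol/L plus HbA1C < 6.5" (per cent). Section 2.1 gives the reason: "In order to rule out confounding factors and meet the ethical standards to the maximum extent, this study excluded patients with overt diabetes". It then describes a similar earlier trial in which "diabetes patients were excluded because various diabetes treatments made it difficult to match the two groups".

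**Drugs the article itself says act on the liver.** From the Introduction: "The traditional treatment includes pioglitazone, a type of insulin-sensitizing agent, which could improve liver biochemical and histological parameters" (the sentence goes on to say in patients with NASH), and "liraglutide is a type of glucagon-like peptide 1 receptor agonist, which could resolve definite NAFLD and prevent the progression of fibrosis". The Introduction also faults an earlier statin trial because "the other oral drugs like Vitamin C and Vitamin D were simultaneously taken, which might become the confounding factors".

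**Design.** "The RNAFH study is a prospective randomized, single-center, open-label study", with 20 patients on rosuvastatin and 20 on blank control. The primary end point is the change in IHCL from baseline to week 52, compared by a two-sample t-test (Section 3).

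**The concern.** An eligibility line has to give the same decision whoever reads it, and this one does not. Screening staff who take it at its word would enrol a fibrate user. Staff who carry the 'not' across would turn the same patient away.

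Lipid drugs matter directly here. TG, HDL-C and LDL-C are secondary end points, and statins are the class under test. A recent statin user let in through the fibrate half could have baseline lipids that still reflect earlier treatment. The article also presents itself as keeping confounders out and criticises an earlier trial over drugs taken alongside the study treatment.

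The lesser question is whether the diabetes criterion fully serves the aim in Section 2.1. It tests history and glycaemia, so a patient without diabetes who takes pioglitazone or liraglutide passes it as printed.

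**Working it through.** **1. The two readings of the lipid-drug line.** Let A be no statin in the past 3 months and B be current fibrate use. As printed, the line is A or B. The probable intent is A and not B.

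| Patient | As printed (A or B) | Neither drug (A and not B) |
|---|---|---|
| No recent statin, no fibrate | meets | meets |
| No recent statin, on fibrate | meets | fails |
| Recent statin, on fibrate | meets | fails |
| Recent statin, no fibrate | fails | fails |

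The readings disagree in two of the four rows, which are all the fibrate users. As printed, a recent statin user is refused unless also on a fibrate. That is hard to defend as a design, which is why 'neither' is the likely intent. No exclusion item changes rows two or three.

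Adding a second 'not' but keeping 'or' would still leave doubt. Taken as alternatives, not A-drug or not B-drug would admit anyone not on both.

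**2. Glucose-lowering drugs, side by side.** Section 2.1 gives this trial's reasons as confounding factors and ethics. The treatment-matching reason is attached to the cited trial. The criterion in Section 2.3 does deliver a population without overt diabetes, so nothing is contradicted. What remains is a gap between the printed list and the broader aim.

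**3. Can the size be worked out?** The plan's own figure first. With difference 7.28, SD 3.95, two-sided α 0.05 and power 0.90 (Section 3), n per group = 2 × (1.960 + 1.282)² × 3.95² / 7.28² = 6.2, so 7, as stated. The exact t-test gives 7.30, so 8. Neither comes near the 20 planned, and this point disputes no sample-size figure.

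The article gives neither the number of users nor a drug effect on IHCL. Both are pure assumptions below.

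- Assume 4 users among 40. The chance of a 2:2 split is C(20,2)² / C(40,4) = 36100 / 91390 = 0.395. The chance of 3:1 either way is 0.499, and of 4:0 either way 0.106.
- Assume a user's IHCL falls by an extra D = 3 to 7.28 points (7.28 being the plan's weight-loss figure). The shift in the between-arm difference is (excess users / 20) × D. An excess of 2 gives 0.30 to 0.73, and an excess of 4 gives 0.60 to 1.46.
- The standard error is 3.95 × √(2/20) = 1.25, or 3.95 × √(2/16) = 1.40 with 16 per arm after 20% dropout.
- With 10% users, SD = √(3.95² + 0.1 × 0.9 × D²) = 4.05 to 4.51. With 20% users (8 of 40) it reaches at most 4.91. The exact t-test for a difference of 7.28 then needs 8 to 11 per arm, still below 20.

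These figures lean high. The end point is a change from baseline, so a patient stable on a drug carries its effect in both scans, and only recent starters could show anything like the full D. The shift and the SD increase describe the same variation and must not be added.

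**The case against.** **The fibrate line is only a slip, and everyone will read it as 'neither'.** That is the natural reading, and nothing suggests that fibrate users were meant to be let in. A reader might infer a deliberate route into the trial, but the documents do not support that. What stands is that the printed rule says something else and no other item corrects it. Condensation for a journal does not explain it, since the words are there and are ambiguous.

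**The glucose-lowering half is an absence, not an error.** This largely succeeds. A list of barred concomitant drugs is something an article may leave to the full protocol, which is not shown. The Introduction also says that NAFLD has no widely accepted drug treatment, and nothing shows that such users are in this population. Its criticism of vitamins in an earlier trial does not say whether they were study treatment or background use, so it cannot be shown that this trial repeats that weakness. What remains is a request to reconcile, because Section 2.3 introduces its list as the criteria and does go down to individual drug classes.

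**Randomisation deals with baseline use.** It does so on average, and the t-test's standard error already allows for chance imbalance. The tempting claim that the primary result would be biased therefore fails. In an open-label trial, drugs started unequally after allocation could bias it, but that is not what these criteria govern.

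**Conclusion.** The point holds for the lipid-drug line: an operative eligibility rule is wrong as written, or at best ambiguous, and its two readings give opposite decisions for any fibrate user. This rests on the printed text alone.

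The effect on the results is chance imbalance and some added variance, not systematic bias, and its size cannot be derived from the documents. At the planned difference of 7.28 the 20 per arm remain enough even under the assumed values above.

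The glucose-lowering point is secondary. A reader might infer that the criteria contradict Section 2.1. They do not: the criterion implements the exclusion of overt diabetes, and the reason about diabetes treatments belongs to the cited trial.

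**What to change.** 1. Reword the lipid-drug line in Section 2.3 so that it has one meaning and agrees with the aim in Section 2.1. If 'neither' was intended, the clearest form is two separate exclusion items: statin use within the past 3 months, and current fibrate use.
2. Section 2.4 refers to a patient already enrolled. For enrolled patients, check which reading was applied. If any fibrate user or recent statin user entered, repeat the primary comparison without them as a sensitivity analysis.
3. Reconcile the diabetes criterion with the rationale in Section 2.1, and record baseline use of glucose-lowering drugs. Which drugs to allow, and over what look-back, is for the investigators to decide.

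The cost is a short amendment, a check of screening records, one baseline item and at most one extra analysis. No visit or test is added. If the literal reading has been in use, a few screened patients may no longer qualify.

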### 2.4. Study Procedure

The study flow is shown in Figure 1. Patients will be randomly assigned to receive rosuvastatin 10 mg/day (*n* = 20) or blank control (*n* = 20). All patients will be given lifestyle improvement suggestions at baseline. ^1^H-MRS will be conducted at the baseline and the 52nd week; the images of ^1^H-MRS are shown in Figure 2. Physical examination and ALT, AST, TBIL, eGFR (EPI), CK, Cr, ACR (urine), TSH, FBG, FINS, LDL-C, HDL-C, TC, TG, and FFA will be measured at the baseline, 4th, 16th, 28th, and 40th week, and 52nd week. Lifestyle improvement suggestions include reducing oil consumption, weight loss, increasing aerobic exercise, smoking cessation, and alcohol reduction. The lifestyle intervention should be recorded at each visit, including food frequency questionnaires and amount and intensity of exercise. The change of IHCL will be calculated by Siemens SKYIA 3.0 T using HISTO-MRS placed on the same region of right lobe of liver at baseline and at end point. Figure 2 showed the ^1^H-MRS images of one patient enrolled in this study with IHCL > 10%.

## 3. Determination of Sample Size and Statistical Analyses

The primary end point is the change of IHCL and there is no similar study for reference. Cowin et al. [29] conducted a study using ^1^H-MRS to evaluate IHCL change after a six-month weight loss program in overweight subjects. The IHCL by ^1^H-MRS before and after weight loss program were 15.2 ± 5.64% and 7.92 ± 6.18%, respectively. The change of IHCL was 7.28 ± 3.95%. We hypothesised that the effect of rosuvastatin (10 mg/d) on IHCL will be comparable to the effect of weight-loss. According to the study described above, we take 7.28 as the difference of mean of the change between two groups and 3.95 as the standard deviation. As two-side *α* = 0.05, *β* = 0.10, and actual power is 0.9, the sample size needed for each group is 7. Based on this assumption, the number of patients needed to be enrolled is 14, and considering the dropout rate of 20%, at least 20 patients with a total enrollment of 40 are needed.

IHCL change from baseline to 52 weeks after treatment will be compared between the control group and the rosuvastatin group using the two-sample *t*-test. Changes from baseline for the following parameters will be compared between the control group and the rosuvastatin group at 4 weeks, 28 weeks, and 52 weeks including LDL-C, HDL-C, TC, TG, FFA, ALT, AST, eGFR, HbA1c, CK, FBG, UACR, and HOMA-IR. If it is deemed necessary, effect of rosuvastatin on these parameters will be assessed using mixed model for longitudinal data. Due to the feasibility nature of this study, exploratory analysis may be performed. Continuous variables were described by mean and standard deviation, or by median and range; two-sided level of significance of 0.05 was applied to general comparison.

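### The enrolment of 40 does not follow from 7 per group and 20% dropout: those inputs give 18 patients, and the plan does not state what 40 can detect

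*Protocol article*

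**What the plan says.** All inputs are in Section 3 of the protocol article. The effect and spread come from a six-month weight-loss study: "we take 7.28 as the difference of mean of the change between two groups and 3.95 as the standard deviation". The error rates follow ("As two-side *α* = 0.05, *β* = 0.10"), and the result is given as "actual power is 0.9, the sample size needed for each group is 7". The text then says "the number of patients needed to be enrolled is 14", and the dropout step closes the chain: "considering the dropout rate of 20%, at least 20 patients with a total enrollment of 40 are needed".

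Section 2.4 shows that the 20 is a per-group figure: "Patients will be randomly assigned to receive rosuvastatin 10 mg/day (*n* = 20) or blank control (*n* = 20". Section 2.3 also gives 40 as the number to be enrolled. The primary analysis in Section 3 compares the change in IHCL between groups, which "will be compared between the control group and the rosuvastatin group using the two-sample *t*-test".

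**The concern.** The plan presents 40 as the outcome of a dropout adjustment, but an adjustment for 20% loss raises a sample size by a quarter, and here it rises nearly threefold. Rounding cannot explain this.

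What is at stake is the justification of the enrolment rather than the validity of the primary test. Someone judging whether 40 patients are warranted is told that this number is needed, when the stated inputs support about half of it. The plan says that no similar study was available and borrows its effect from a weight-loss programme. The smallest effect that the actual sample size could detect is therefore useful information, and it is not given.

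**Working it through.** **Inputs (protocol article, Section 3):** difference in mean change 7.28; SD 3.95; two-sided alpha 0.05; power 0.90; 20% dropout; two-sample t-test. Allocation is 1:1 (Section 2.4).

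**Step 1. Reproduce the 7 per group.** Normal approximation:

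n = 2 × [(1.960 + 1.282) × 3.95 / 7.28]² = 6.19, rounded up to 7 per group, 14 in total.

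The plan's figure reproduces.

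**Step 2. Apply the stated dropout.**

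| Starting n | n / (1 − 0.20) | n × 1.20 |
|---|---|---|
| 7 per group | 8.75, so 9 | 8.4, so 9 |
| 14 in total | 17.5, so 18 | 16.8, so 17 |

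Both conventions give 9 per group. Neither comes near 20 per group or 40 in total.

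**Step 3. Dropout implied by the stated figures.** 1 − 14/40 = 1 − 7/20 = 0.65, so 65% rather than 20%.

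**Step 4. Power of the planned test (noncentral t, standardised difference 7.28/3.95 = 1.843).**

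| Per group | Power |
|---|---|
| 7 | 88.5% |
| 8 | 92.8% |

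The smallest n reaching 90% is 8 per group. With 20% dropout, 8/0.8 = 10 per group, 20 in total. This is still half of 40.

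**Step 5. What 40 enrolled delivers.** With 20% dropout, 20 × 0.8 = 16 completers per group. By the noncentral t:

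- SD 3.95, difference 7.28: power 99.9%.
- SD 3.95: 90% power for a difference of 4.68, and 80% power for 4.04.
- SD 6.18 (the after-programme SD of IHCL in the cited study), difference 7.28: power about 90%.

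The last line shows how much the answer depends on the SD. The 3.95 comes from change over a six-month weight-loss programme in overweight subjects, while this trial measures change over 52 weeks in patients with IHCL above 10%.

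**The case against.** The strongest defence is that the error does no harm. Enrolment of 40, allocation of 20 and 20, and the primary test agree wherever they appear. On the plan's own assumption, 16 completers per group give 99.9% power. A larger trial also guards against an optimistic effect or SD, and a reader who accepts the inputs can compute the detectable difference. Most of this stands, and it limits the point to the derivation and its transparency. It does not rescue the sentence, which says that 40 is needed because of 20% dropout. It mentions no safety margin, and the other sections only repeat the number.

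It might be said that a journal article condenses the full protocol. But the article does not leave the derivation out. It states every step, and the last step is wrong.

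Three stronger readings are tempting and are not supported:

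- A reader might infer that the sample size, dropout rate and power contradict one another. They do not: 40 enrolled, 20% loss and at least 90% power are compatible. Only the claim that the first follows from the second fails.
- A reader might count the 7 per group as a second error. It is a correct normal-approximation result, its t-test power is 1.5 points below the stated 0.9, and it has no effect on a trial that enrols 20 per group.
- A reader might infer how the 20 arose. A t-test total of 20 could have been taken as a per-group figure and doubled. Alternatively, SD 6.18 in the normal approximation gives 15.1, so 16 per group, and 16/0.8 = 20. The document supports neither, since it states SD 3.95 and 7 per group.

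**Conclusion.** The point holds as an error in the sample-size derivation. The stated inputs give 18 patients, or 20 if the t-test is used for the starting n, against 40 stated: an excess of about twofold with no reason given. The discrepancy follows from the plan's own figures and needs no outside assumption.

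The trial is not underpowered for its stated assumption, and nothing here calls the primary test into question. What a reader lacks is a true account of why 40 patients are enrolled and what difference they can detect. The detectable difference of about 4.7 points at 90% power rests on SD 3.95, equal group sizes and exactly 20% loss. It would be larger with a larger SD.

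**What to change.** Keep enrolment at 40 and rewrite the sample-size paragraph in Section 3:

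1. Remove the statement that 40 follows from 20% dropout.
2. Correct the dropout step to 9 per group, 18 in total. Preferably base it on the planned t-test: 8 evaluable per group (92.8% power), then 10 per group and 20 in total after 20% dropout.
3. State the sponsor's real basis for 40 if there was one, such as a smaller difference, a larger SD or a higher expected loss.
4. If there was none, state what 40 delivers. Suggested wording: *Forty patients (20 per group) will be enrolled. With 20% dropout, 16 per group give 99.9% power for a difference of 7.28 percentage points and 90% power for about 4.7, two-sided alpha 0.05, if the SD of the change is 3.95. If the SD is 6.18, power for 7.28 is about 90%.*

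The cost is one reworded paragraph. Enrolment, allocation and analysis are unchanged.

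### The primary t-test on IHCL change makes no use of baseline IHCL; prespecified baseline adjustment would be a nearly free, probably modest improvement on a valid test

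*Protocol article*

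**What the plan says.** Section 3 of the protocol article names the primary test: "IHCL change from baseline to 52 weeks after treatment will be compared between the control group and the rosuvastatin group using the two-sample" *t*-test. No covariate is attached to it. The mixed model mentioned later in that section is optional and is tied to the lipid, glucose and safety measures, not to IHCL.

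Baseline IHCL is available for everyone. Section 2.3 requires IHCL above 10% by ^1^H-MRS for entry, and Section 2.4 schedules ^1^H-MRS at baseline and week 52.

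The planning figures come from a six-month weight-loss study whose IHCL values "before and after weight loss program were 15.2 ± 5.64% and 7.92 ± 6.18%, respectively". From it, "we take 7.28 as the difference of mean of the change between two groups and 3.95 as the standard deviation". The article also concedes that "The primary end point is the change of IHCL and there is no similar study for reference". Planned enrolment is 20 per arm, with 20% dropout allowed for.

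**The concern.** A *t*-test on change is the same as regressing week-52 IHCL on group with the baseline coefficient fixed at 1. If the true slope is below 1, patients who start with more liver fat tend to lose more of it whichever arm they are in. The arm that happens to start higher then looks somewhat better for a reason unrelated to treatment. With 40 patients such an imbalance can easily arise, and an adjusted analysis added after the data are seen would look chosen by its result.

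What is at stake is some precision, and protection of the primary estimate against an observed baseline difference.

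**Working it through.** **Inputs** (protocol article, Section 3): baseline SD s0 = 5.64; follow-up SD s1 = 6.18; change SD sd = 3.95; planned difference 7.28; two-sided alpha 0.05; power 0.90; 20 per arm. With 20% dropout, 20 × 0.8 = 16 per arm complete.

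**1. The plan's own figure.** n per group = 2 × (1.960 + 1.282)² × (3.95/7.28)² = 6.2, rounded up to 7. The stated 7 reproduces by the normal approximation. The exact *t* calculation gives power 0.885 at 7 per group and 0.928 at 8.

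**2. Correlation and slope implied by the SDs.**
- r = (s0² + s1² − sd²)/(2·s0·s1) = (31.81 + 38.19 − 15.60)/69.71 = 0.780
- Slope of week-52 on baseline = r·s1/s0 = 0.780 × 6.18/5.64 = 0.855
- Share of a baseline difference left in the change score = 1 − 0.855 = 0.145

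**3. Effect of a chance imbalance.** The standard error of the baseline difference is 5.64 × √(2/n).
- 20 per arm: 1.78 points. A one-SE imbalance shifts the estimate by 0.145 × 1.78 = 0.26 points, against a standard error of 3.95 × √(2/20) = 1.25.
- 16 per arm: 1.99 points, a shift of 0.29, against a standard error of 1.40.

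**4. Precision.** The ANCOVA residual SD is 6.18 × √(1 − 0.780²) = 3.86. The large-sample variance ratio, ANCOVA to *t*-test, is (3.86/3.95)² = 0.957. Estimating the slope costs a factor of about 1 + 1/(N − 4), where N is the total analysed.

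| Analysed | Factor | Variance ratio |
|---|---|---|
| 40 | 1.028 | 0.984 |
| 32 | 1.036 | 0.991 |
| 14 (the calculated minimum) | 1.100 | 1.053 |

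A simulation of 40,000 trials per size gave 0.983, 0.995 and 1.053, with mean error close to zero for both methods.

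**5. Allowing for the entry cut-off.** Assume a normal baseline (mean 15.2, SD 5.64) truncated at 10. The baseline SD falls to 4.39. The change variance becomes 3.86² + 0.145² × 4.39² = 15.34, so the large-sample ratio is 14.93/15.34 = 0.974. Times the factors above, the ratio is 1.00 at 40 and 1.01 at 32. The one-SE shift at 16 per arm falls to 0.145 × 4.39 × √(2/16) = 0.23 points.

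**6. If the 52-week correlation is lower** (assumption; s0 and s1 kept, no truncation).

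| r | Implied change SD | Large-sample ratio | Ratio at 32 | One-SE shift at 16 per arm |
|---|---|---|---|---|
| 0.6 | 5.3 | 0.868 | 0.90 | 0.68 |
| 0.5 | 5.9 | 0.815 | 0.84 | 0.90 |

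The shift is (1 − r × 6.18/5.64) × 1.99. The large-sample gain disappears where the slope reaches 1, at r = 5.64/6.18 = 0.91.

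**7. Power.** At 7.28 it exceeds 0.99 with either method at 16 or 20 per arm. For an assumed true difference of 3 points at 20 per arm it is 0.655 with ANCOVA and 0.648 with the *t*-test.

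**The case against.** The strongest reply is that nothing here is wrong. The *t*-test on change matches the stated endpoint (Section 2.2) and the SD used for sample size. Its standard error already includes the variation from baseline imbalance, so its type I error is intact. On the plan's figures the gain is 1 to 2%, and it vanishes once the 10% cut-off is allowed for. The larger gains need correlations that contradict the plan's change SD of 3.95. The slope of 0.86 itself comes from a study the plan does not regard as similar. An unseen analysis plan may add covariates.

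Most of this stands, and it rules out two stronger readings. A reader might infer that ANCOVA is never less efficient. That is a large-sample result: at 7 per arm it loses about 5% here, and with truncation it is level or about 1% worse at the planned size. A reader might also infer that the *t*-test is biased and that adjustment removes the bias. Under randomisation the *t*-test is unbiased. ANCOVA removes only the error conditional on an observed baseline imbalance, assuming a linear relation.

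Two parts of the reply do not defeat the recommendation. The article does not leave the primary test open; it names an unadjusted one. And doubt about the reference study works in both directions: it covered six months of weight loss, so a lower correlation at 52 weeks on a different intervention is possible, and adjustment would then pay materially.

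**Conclusion.** The point holds as a low-cost improvement, not as an error that threatens the result. The plan fixes an unadjusted primary test although the baseline value is to hand. On its own SDs, about 14% of a chance baseline difference enters the estimate, roughly 0.26 to 0.29 points for a one-SE imbalance, or about a fifth of the standard error (0.26/1.25 and 0.29/1.40). The precision gain is 1 to 2% at the planned size, and nil to a loss of about 1% under a normal baseline truncated at 10%. It rises to about 10% or 16% at 32 completers if the correlation is 0.6 or 0.5.

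The balance favours adjustment: little to lose on the plan's figures, more to gain if the correlation is lower. Were the slope exactly 1, the loss would be the full factor from step 4, about 3.6% at 32 completers.

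The figures assume a linear relation with a common slope in both arms, and that the reference study's SDs carry over. The lower correlations are assumptions, not figures from the documents.

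**What to change.** Prespecify as the primary analysis a linear model of week-52 IHCL (or its change) on randomised group and baseline IHCL. Report the adjusted difference with its 95% confidence interval and two-sided p-value. Keep the two-sample *t*-test on change as a sensitivity analysis, and adjust the secondary continuous endpoints for their own baselines in the same way.

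This takes a sentence or two of analysis wording, no new data or visits, and one degree of freedom. It should be settled before outcome data are examined.
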